**Local reactions:**

- Size of erythema (at site of injection) in cm
- Size of swelling/ induration (at site of injection) in cm
- Pain/Tenderness (at site of injection)
- Pruritus (at site of injection)
- Eccymosis (at site of injection) in cm

**Systemic Reactions:**

- Fever-Body temperature (and location of measurement)
- Fatigue/malaise
- Myalgia
- Arthralgia
- Chills
- Nausea/Vomiting
- Headache

### 9.3.6 Unsolicited Adverse Events

Unsolicited adverse events are any AEs that occur any time after the vaccine/placebo is given (temporally related to study product), whether or not deemed “related” to the product, and are not solicited (not specifically asked of the participant). Unsolicited AEs can be observed by study staff while the participant is at a clinic for a study visit or reported by the participant at any time. Any solicited sign or symptom starting after 7 days post- each vaccination will be recorded as an “unsolicited AE”.

### 9.3.7 Serious Adverse Events

An SAE is defined as an AE that meets one of the following conditions:

- Death.
- Life-threatening (participant at immediate risk of death.) (The term “life-threatening” in the definition of “serious” refers to an event in which the patient was at risk of death at the time of the event; it does not refer to an event that hypothetically might have caused death if it were more severe).
- Requires inpatient hospitalization or prolongation of existing hospitalization.
- Results in congenital anomaly/birth defect. (Only in the case of a woman becoming pregnant during the study period after administration of at least one injection of study product. All pregnancies must be followed to term and outcome reported to Butantan and regulatory agencies.)
- Results in a persistent or significant disability or incapacity.
- Important medical events that might not result in death, be life-threatening, or require hospitalization might be considered SAEs when, based upon appropriate medical judgment, the event might jeopardize the well-being of the participant and require medical or surgical intervention to prevent one of the outcomes listed above. (Medical and scientific judgment should be exercised in deciding whether reporting these events is appropriate.)

All SAEs occurring within 4 weeks of each study vaccination must be reviewed and evaluated by a study clinician (SAE relationship to study vaccine must be evaluated and recorded on an SAE form and reported, as specified in Section 9.4). All such SAEs should also be followed until satisfactory resolution or until the investigator deems the event to be chronic or the participant to be stable.

### 9.3.8 Procedures for Out-of-range Laboratory Test Values

Out-of-range laboratory values and AEs. To the extent possible, all reference ranges for clinical laboratory test results will be pre-specified. The site staff will follow the Toxicity Table (Table 5). Laboratory values that are out-of-range will not be considered an AE unless they qualify as a Grade 2 or above on the Toxicity Table. The reference ranges for the laboratory will be taken in to consideration when determining out of range results.

Out-of-range test values may be considered an SAE if two circumstances are met:

1. the value rises to the level of Potentially Life-threatening (Grade 4), and
2. the event is determined by the Principal Investigator to pose an immediate risk of death.

A Grade 4 laboratory result does not, in and of itself, constitute an SAE. Grade 4 places a laboratory value as a potentially life-threatening event, but a Grade 4 laboratory result should not be reported as an SAE unless the PI has determined that it does, in fact, pose an immediate risk of death.

Assessing relatedness and clinical significance of out-of-range laboratory values: All laboratory results should be reviewedAny laboratory finding Grade 2 and above is regarded as an AE. The investigator will assess relatedness and clinical significance for these findings.

Clinical judgment always should be used to determine whether a laboratory result requires additional follow up. However, the investigator should redraw any Grade 2 or above laboratory result that is deemed clinically significant at an unscheduled visit to check if the result has normalized.

Any Grade 2 or above laboratory value that is clinically significant and has not returned to normal or stabilized by day V2+194 should be marked by the investigators as “continuing” or “unresolved.” The investigator should assure that the participant is referred for appropriate medical follow-up, if indicated.

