# Assessment of Safety and Adverse Events

## 9.1 Definition and Categorization of AEs

The primary objective of this study is to evalute the safety profile and immunogenicity of the vaccine candidates. An AE (adverse event) is defined as any untoward medical occurrence in a participant administered an study product, which may or may not bear a causal relationship with this study injection. An AE can therefore be any unfavorable and unintended sign (including an abnormal laboratory finding), symptom, or disease temporally associated with the use of a medicinal product, whether or not considered related to the medicinal product. A subset of AEs, those commonly observed after influenza vaccine administration are described in the Participant Diary and will be specifically requested for 7 days post each study injection. Those AEs are termed “solicited” and will be evaluated for potential relationship with study product. Out-of-range laboratory abnormalities observed after study injections will be graded according to the grading table (see Table 5) and their clinical significance and potential relationship to study product assessed. Only those laboratory abnormalities greater than Grade 1 will be recorded as AEs.

All AEs should be graded using the Tables for Grading AEs (Tables 4, 5 and 6). These tables contain list of specific clinical and laboratory safety measurements of interest to the study. All clinical safety evaluations must be made by a qualified physician.

Any clinical sign or symptom or laboratory finding at any time-point might be categorized as an SAE if it meets the criteria established.

All adverse events will be MedDRA coded.

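### Protocol 9.3.8 judges laboratory abnormalities by a narrower test of seriousness than the SAE definition in 9.3.7, so some could be missed as SAEs

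*Protocol*

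**What the plan says.** **General definition (Protocol 9.3.7).** "An SAE is defined as an AE that meets one of the following conditions". One of the conditions is: "Requires inpatient hospitalization or prolongation of existing hospitalization". It carries no grade threshold and does not ask for a risk of death. A further condition rests on medical judgement: "Important medical events that might not result in death, be life-threatening, or require hospitalization might be considered SAEs".

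**Laboratory findings are adverse events.** Section 9.1 states: "An AE can therefore be any unfavorable and unintended sign (including an abnormal laboratory finding), symptom, or disease". Sections 9.1 and 9.3.8 both set the recording threshold at Grade 2 and above.

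**Special rule for laboratory values (Protocol 9.3.8).** "Out-of-range test values may be considered an SAE if two circumstances are met". The first circumstance is "the value rises to the level of Potentially Life-threatening (Grade 4), and"; the second is that the principal investigator finds an immediate risk of death. The section then says that a Grade 4 value does not by itself make an SAE, and goes on: "a Grade 4 laboratory result should not be reported as an SAE unless the PI has determined that it does" in fact carry that immediate risk.

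**Where the classification is used.** SAEs over the study period are a secondary safety endpoint (3.1). All SAEs go to the sponsor within 24 hours of site awareness (9.4.1). The SAE category in 11.5 mentions Grade 4 laboratory findings considered life-threatening. The halting rules in 9.6 exclude laboratory-related SAEs from the single-SAE trigger and refer to 9.3.8 for their handling.

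**The concern.** Two sections test the seriousness of the same event differently. Section 9.3.7 needs one condition out of several. Section 9.3.8 needs two conditions together, and the only 9.3.7 condition they resemble is the life-threatening one. A participant admitted because of an isolated laboratory abnormality, with no immediate danger to life, would be counted or not counted as an SAE depending on which section the site applied.

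At stake are the completeness and uniformity of a secondary safety endpoint, and prompt sponsor notification, in a multicentre trial that the protocol describes as the first human use of these antigen and adjuvant combinations. The event would still be in the data as an AE. What could be lost is its classification as serious.

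**Working it through.** No figure in the protocol bears on this, so there is nothing to recompute. The check sets the two rules side by side for an event recorded **only** as a laboratory abnormality.

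**Inputs**
- Rule A (9.3.7): serious if at least one listed condition is met.
- Rule B (9.3.8): may be serious if Grade 4 **and** the principal investigator finds immediate risk of death; a Grade 4 result without that risk is not to be reported as an SAE.
- Scope: laboratory findings of Grade 2 or above are AEs (9.1, 9.3.8), so Rule A applies to them on its face.

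| Laboratory AE | Rule A (9.3.7) | Rule B (9.3.8) | Agree? |
| --- | --- | --- | --- |
| Grade 4, immediate risk of death | SAE | Both circumstances met | Yes |
| Grade 4, no 9.3.7 condition met | Not an SAE | Not an SAE | Yes |
| Grade 4, admitted, no immediate risk of death | SAE | Expressly barred | **No** |
| Grade 4, judged medically important, not admitted, no immediate risk of death | SAE if so judged | Expressly barred | **No** |
| Grade 2 or 3, admitted, no immediate risk of death | SAE | Fails both circumstances | **No** |
| Grade 2 or 3, judged medically important, no immediate risk of death | SAE if so judged | Fails both circumstances | **No** |

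**Two illustrations from the protocol's own grading tables**
1. Table 5 assigns creatinine Grade 4 when it exceeds 2.5 mg/dL or when dialysis is needed. If such a participant is admitted and the investigator finds no immediate risk of death, 9.3.7 gives an SAE and 9.3.8 says not to report one.
2. In Table 6, and for several events in Table 4, hospitalisation raises a clinical event to Grade 4. Table 5 has no such clause. A Grade 3 laboratory AE that leads to admission therefore stays Grade 3 and fails the first circumstance of 9.3.8.

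**Strength of the wording.** The conflict is firmest for Grade 4, where 9.3.8 contains an explicit instruction not to report. For Grades 2 and 3 it follows from failing the stated conditions; no sentence forbids reporting them.

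**Route to the endpoint.** The secondary endpoint in 3.1 and the reporting duty in 9.4.1 both take as input whatever has been classified as an SAE. An event kept out at that step by 9.3.8 reaches neither. It still enters the 11.5 analysis of other adverse events, which covers abnormal laboratory findings from Days 7 and 35.

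**The case against.** The best defence is that 9.3.8 only warns staff not to confuse a grade label with seriousness. Its lead-in is permissive and does not say that this is the only route. The restrictive sentence follows one saying that Grade 4 alone is not an SAE, and 9.3.7 likewise insists that life-threatening means actual and not hypothetical danger. On this view 9.3.8 is about a test value and 9.3.7 about the event, so an admission is judged under 9.3.7 anyway. This reading is reasonable and may be what was intended. But the warning is already complete in the sentence before. The next one goes further, makes immediate risk of death the condition for reporting a Grade 4 result, and mentions no exception for the other 9.3.7 conditions.

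Several stronger readings are tempting but are not supported:
- **That 9.1 is also contradicted.** It says: "Any clinical sign or symptom or laboratory finding at any time-point might be categorized as an SAE if it meets the criteria established". It does not say which criteria, so it fits either section.
- **That 11.5 removes these events from the SAE analysis.** Its list begins with all SAEs, and the laboratory sentence is worded as an inclusion. It excludes nothing, though it names only the narrow class.
- **That nearly every 9.3.7 condition is disabled for laboratory findings.** Congenital anomaly and persistent disability hardly describe a test value, and a fatal abnormality would already carry a risk of death. Hospitalisation is the firm case; medical importance is discretionary.
- **That the conflict decides whether the trial halts.** Section 9.6 excludes laboratory-related SAEs from the single-SAE trigger under either definition, and gives laboratory abnormalities their own triggers.
- **That Table 8 is undermined.** It concerns the chance of seeing at least one safety event of any kind and is not specific to SAEs.

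It is also true that a participant admitted with a recorded clinical diagnosis enters as an SAE through 9.3.7 whatever 9.3.8 says. Further SAE review details are left to a Safety Reporting Manual that is not at hand.

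**Conclusion.** The conflict between 9.3.7 and 9.3.8 is real and should be reconciled. It is confined to events recorded solely as laboratory abnormalities, with admission or judged medical importance but no immediate risk of death, at sites that apply 9.3.8 literally. Such events could be missed in the secondary SAE endpoint and in 24-hour reporting, while still being captured and analysed as AEs.

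The protocol gives no rate from which to estimate how many there would be. In healthy adults aged 18 to 59 the number is probably small. A reader might infer that laboratory SAEs will be systematically left out of the endpoint. The text does not show that: the loss depends on how sites read 9.3.8 and on whether a clinical diagnosis is recorded alongside the value. Nor does differing site practice by itself imply a biased comparison between arms, since randomisation is stratified by site and assessors are blinded.

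**What to change.** Reconcile 9.3.8 with 9.3.7 so that one definition of seriousness feeds the SAE endpoint. For example:
- In 9.3.8, keep the statement that a Grade 4 result alone is not an SAE, and replace the two joint circumstances and the reporting bar with a statement that a laboratory AE meeting any 9.3.7 condition is an SAE and is counted as one.
- In 11.5, align the laboratory sentence under SAEs, so that it no longer names only Grade 4 life-threatening findings.
- In 9.6, check that the cross-reference to 9.3.8 still makes sense once 9.3.8 is reworded. This is a matter of consistency; no change to the halting thresholds is suggested.

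The cost is a wording change, matching text in the Safety Reporting Manual if it repeats the narrow rule, and possibly a few more SAE forms. Sample size, visits and collected data are unaffected.

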## 9.4 Reporting Procedures

All participants must be told on definitions of AE and SAE and how they must be reported to the PI or clinical staff according to sections 9.1 and 9.3 in this protocol. ICF and Participant Diary must contain specific information on whom and what time to proceed such reports or to clarify doubts on AEs and SAEs

### 9.4.1 Serious Adverse Events (SAEs)

All SAEs must be documented and reported to Butantan or its designee, even if the investigator considers that the SAE is not related to treatment. The study clinician will complete a **Serious Adverse Event (SAE) Form** within the following timelines of such events:

- All SAEs regardless of relationship to the study products, will be reported to the Sponsor within 24 hours of site awareness.

Butantan will be primarily responsible for medical monitoring of serious adverse events documented by the investigator. Details for review of serious adverse events and other unanticipated problems will be in Safety Reporting Manual drafted prior to study initiation.

### 9.4.2 Adverse Events of Special Interest (AESIs)

All AESIs must be documented in a specific AESI report form, even if the investigator considers that the AESI is not related to treatment. If the AESI is also a SAE it should follow reporting timelines described in 9.4.1. Details for review of AESI will be in Safety Reporting Manual drafted prior to study initiation.

### 9.4.3 Reporting of AEs

Collected SAEs and AEs will be reported to responsible ethical review committees. An SOP or other written procedures for reporting to the responsible committees will be developed with reporting requirements and timelines prior to study initiation. It will be the investigator’s responsibility to assure that all reportable events are reported to the Sponsor and to the ethical committee. The Sponsor will be responsible for reporting to the regulatory agency.

### 9.4.4 Other Unexpected Issues/Unanticipated Problems

During study process, if there are any problems related to the trial (unanticipated problems), the Principal Investigator(s) is responsible for reporting to Butantan to discuss reasonable ways of handling the problem. The Principal Investigator(s) is responsible for reporting any unanticipated problems that affect the health, welfare or rights of study participants or that may impact the integrity of the study data to the ethics committees involved in the review of the research. The Principal Investigator(s) should maintain written documentation of all unanticipated problems and their reporting and resolution.

### 9.4.5 Reporting of Pregnancy

Although women are tested for pregnancy before each vaccination and are instructed to use effective birth control by Day 60 after the last dose of vaccine, it is possible for a woman to report a pregnancy during that time. Any pregnancy occurring within 60 days after the last vaccination in any participant of this study should be reported in a Pregnancy Report CRF. Relevant conditions about previous pregnancies should be reported in this CRF, if applicable. The initial report of the current pregnancy should be done in the same CRF and the correspondent fields filled in throughout the prenatal follow-up. The investigator should provide the sponsor with monthly information regarding the results of the exams and clinical conditions of the participant during the prenatal period. Any case of spontaneous abortion or stillbirth should be considered as a severe adverse event (GAS) minimally by the criterion "clinically significant event", which should be reported timely following the guidelines given in item 9.4.1. It is worthy to point out that the outcome of gestation should be reported considering the type of delivery, gestational age and conditions of the newborn, including information on congenital anomalies or birth defects. Information on the health status of the newborn during the first week of life and within forty-two days after delivery should be reported to the sponsor on the same CRF, in accordance with the recommendations of the Brazilian Ministry of Health. Allocation unbliding of those who got pregnant will not occur until the conclusion of the study, unless there is a medical indication.

## 9.5 Duration of Follow up for AE Resolution

All reported AEs should be followed until resolution or stabilization. Participants who have an ongoing study product-related SAE at study completion or at discontinuation from the study will be followed by the PI or his designee until the event is resolved or determined to be irreversible, chronic, or stable by the PI.

## 9.6 Halting Rules

Study enrollment and dosing will be halted and an ad hoc DSMB review/recommendation will be performed if any of the following occur:

Study Halting Events:

1. One or more participant experiences ulceration, abscess, or necrosis at the site of injection associated with product administration.
2. One or more participant experiences laryngospasm, bronchospasm, or anaphylaxis within 24 hours following administration of study product that is associated with product administration.
3. One or more participant experiences a study injection related SAE (excluding laboratory related SAEs, which will be managed as described in section 9.3.8).

1. Two or more participants experience generalized urticaria within 72 hours that is associated with product administration.
2. During the 7 days after each study injection, any of the following occurs across all treatment groups:

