**For the first 100 subjects:**

- - Five or more participants who received at least one study injection to date experience severe (Grade 3/4) study injection-related local reaction of the same category other than measured erythema or induration.
  - Three or more participants who received at least one study injection to date experience a severe (Grade 3/4) study injection-related systemic reaction of the same category (excluding laboratory AEs, which will be monitored separately).
  - Three or more participants who received at least one study injection to date experience a severe (Grade 3) study injection-related abnormality in the same laboratory parameter.
  - Two or more participants who received at least one study injection to date experience a severe (Grade 4) study injection-related abnormality in the same laboratory parameter.

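### A single injection-related laboratory SAE triggers no automatic halt, because Section 9.6 hands it to Section 9.3.8, which contains no halt and no DSMB step

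*Protocol*

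**What the plan says.** Section 9.6 of the protocol lists events that halt enrollment and dosing and require an ad hoc DSMB review. Item 1 of the first list needs a single case: "One or more participant experiences ulceration, abscess, or necrosis at the site of injection associated with product administration". Item 3 also needs a single case, namely any SAE related to the study injection, but with an exception: "excluding laboratory related SAEs, which will be managed as described in section 9.3.8".

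Section 9.3.8 lets an out-of-range laboratory value be an SAE only if it is Grade 4 and, in addition, "the event is determined by the Principal Investigator to pose an immediate risk of death". It states that a Grade 4 value alone is not an SAE. The actions it then assigns to the investigator are to assess relatedness and clinical significance, to "redraw any Grade 2 or above laboratory result that is deemed clinically significant at an unscheduled visit", to mark unresolved values as continuing, and to refer the participant for care. Section 9.3.7 adds that SAEs within 4 weeks of a vaccination "must be reviewed and evaluated by a study clinician".

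Section 9.6 also has reaction-count rules for the 7 days after each injection. The systemic-reaction rules leave laboratory events out: "excluding laboratory AEs, which will be monitored separately". For the first 100 subjects, the laboratory rules are met when two or more participants "experience a severe (Grade 4) study injection-related abnormality in the same laboratory parameter", or when three or more do so at Grade 3. Afterwards the trigger is 2% or more of injected participants with a related Grade 3/4 abnormality in the same parameter.

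**The concern.** The exception in item 3 presents Section 9.3.8 as the place where laboratory SAEs are managed, yet that section manages the participant and not the trial. It names neither a halt nor the DSMB. An exception of this kind would normally serve to avoid stopping a trial for an isolated laboratory outlier. Section 9.3.8 already does that by keeping Grade 4 values out of the SAE category unless the investigator sees an immediate threat to life. What the exception removes from item 3 is the remainder, which is the most serious part.

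The result is an inverted order: one related injection-site abscess stops dosing, while one related laboratory event judged immediately life-threatening may not. According to Section 1.6.1, these antigen-adjuvant combinations have not been given to humans before. Section 11.6 lets enrollment continue during the first DSMB review, and lets second injections go ahead before it is complete, unless a halting rule has been met. An event outside the rules therefore leaves dosing running by default.

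**Working it through.** The protocol states no figure for this point, so the check is a reading of the sections together plus the arithmetic of the count rules.

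**Which rule could one related laboratory SAE meet?**

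| Rule in Section 9.6 | Participants needed | Met by one laboratory SAE? |
|---|---|---|
| Item 1, injection-site ulceration, abscess or necrosis | 1 | No, different event |
| Item 3, related SAE | 1 | No, excluded and sent to 9.3.8 |
| Systemic-reaction counts | 3, later 4% | No, laboratory events excluded |
| Laboratory counts, first 100 subjects | 2 at Grade 4, or 3 at Grade 3 | No |
| Laboratory counts, after the first 100 | 2% of those injected | No, see below |

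**The 2% rule.** Let N be the number of participants injected to date. One case is a proportion of 1/N. At N = 101 this is 1/101 = 0.0099, or 0.99%, below 2%, and it falls as N grows. The smallest count that meets the rule is ceil(0.02 × N):

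- N = 101: 2.02, so 3
- N = 200: 4.00, so 4
- N = 300: 6.00, so 6
- N = 432 (planned total): 8.64, so 9

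One case could complete a count already under way, but it cannot trigger the rule alone. One case would reach 2% only with 50 or fewer participants injected (1/50 = 2%). That would require reading the switch at 100 enrolled subjects as 100 people who had merely consented, as in the Enrolled Population of Section 11.3. This is a strained reading.

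**Illustration under assumed rates.** The protocol gives no rate for a related Grade 4 abnormality in a given parameter, so the rates p below are assumptions. Among 100 subjects, P(at least 1) = 1 − (1 − p)^100 and P(at least 2) = 1 − (1 − p)^100 − 100p(1 − p)^99.

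| Assumed p | At least 1 in 100 | At least 2 in 100 |
|---|---|---|
| 0.1% | 9.5% | 0.5% |
| 0.5% | 39% | 9% |
| 1% | 63% | 26% |

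Across this range a first case is much more likely than a count that would halt the trial. Only some Grade 4 values would also be judged an immediate risk of death, so these figures compare the two triggers and do not estimate how often the gap would be met.

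**Other routes to a stop.**

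- Section 9.4.1: report to the sponsor within 24 hours.
- Section 9.7.1: SAE review as needed by the Study Safety Physician, with an assessment to the DSMB.
- Section 9.7.2: ad hoc DSMB meetings when required.
- Sections 7.6.2 and 9.6: discretionary suspension.

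None of these makes a halt or a DSMB review mandatory after one laboratory SAE.

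**The case against.** The strongest reply is that the sponsor chose this deliberately and that it hardly matters. The exception is explicit, and laboratory events have their own graded rules, with a lower count at Grade 4 than at Grade 3. Participants are healthy, and Grade 2 or higher laboratory values at screening exclude them. Someone whose creatinine, transaminases, bilirubin or blood count put life at immediate risk would ordinarily be admitted. Section 9.3.7 makes admission an SAE criterion of its own: "Requires inpatient hospitalization or prolongation of existing hospitalization". If the exception covers only events that are SAEs by laboratory value alone, such a patient already halts the trial under item 3. The abscess comparison can also be questioned, since an abscess may point to a handling fault with multidose vials mixed at the sites, which is a separate reason to stop after one case. Finally, Section 9.4.1 refers details of SAE review to the Safety Reporting Manual, and Section 9.7.2 refers DSMB activities to its charter. Either could contain the missing step.

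Much of this stands. The exclusion is intended, the affected set is small, and oversight does not disappear. Two points remain. The protocol does not define what makes an SAE laboratory related, so a participant hospitalized for a related Grade 4 platelet count can be read as excluded or as included. And item 3 sends these events to Section 9.3.8, not to the manual or the charter. A halting rule exists so that the stop does not depend on interpretation or discretion.

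**Conclusion.** The concern holds. As written, one related laboratory SAE that is not also counted as a clinical SAE produces no automatic halt and no mandatory ad hoc DSMB review. Every other related SAE halts the trial at 1 participant. A laboratory event needs at least 2 at Grade 4 in the same parameter among the first 100 subjects, and at least 2% of those injected afterwards.

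This is a weak design choice, not a contradiction, and no endpoint, sample size or analysis is affected. The share of laboratory SAEs that would escape item 3 is not given and is expected to be small. The conclusion rests on the protocol text alone. A step in the DSMB charter or the Safety Reporting Manual could close the gap in practice. The change is worth making because it is cheap and the events concerned are judged immediately life-threatening.

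**What to change.** In Section 9.6, item 3, replace the parenthetical exception with: *(including a study injection-related laboratory SAE that meets both conditions of section 9.3.8; Grade 4 laboratory values that are not SAEs remain under the laboratory count rules below)*. Once the exclusion is gone, a laboratory event that is an SAE through hospitalization also falls under item 3, so the term laboratory related needs no definition. Isolated Grade 4 values that are not SAEs still do not stop the trial.

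The cost is one sentence in the protocol, a matching line in the DSMB charter and, rarely, one extra ad hoc DSMB review with a short pause in enrollment and dosing.
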